**Table 1 T1:**
[figure not shown]
Salivary flow values for resting saliva (mL/min).

One aliquot (1 mL) of saliva will be transferred immediately to a small tube (capacity: 5 mL) for titration with hydrochloric acid 0.005 Ne. The tube will be shaken for 15 seconds and buffering capacity will be measured using a glass electrode (Orion) coupled to a pH meter (Procyon 720 A, Procyon, São Paulo, Brazil). Titration under partial carbon dioxide gas is considered the standard method for determining the buffering capacity of saliva. The reading of this test is performed based on the following parameters: pH 3.0 to 4.0 = very low to low buffering capacity; pH 4.5 to 5.0 = intermediate buffering capacity; and pH ≥5.5 = normal/good buffering capacity.^[32]^

The remaining saliva will be stored in Eppendorf tubes and frozen at –20 °C until the analysis of salivary IgA. Concentrations of salivary IgA in all samples will be measured using a commercial Enzyme-Linked Immunosorbent Assay (ELISA) kit (Diametra IgA Saliva Kit, Italy) (Fig. 1). Salivary IgA (μg/mL) in each sample will be calculated using a standard curve obtained from the calibrators in the kit^[19]^ and will be analyzed^[33]^ (Table 2).

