### Saliva collection and analysis

2.8

Saliva will be collected at the dental sector of the CREN in the city of Maceió with the child seated in a dental chair under conventional light. Total resting saliva will be collected between 9 and 11 am (to avoid the influence of circadian rhythm) using the drainage method. The children will have not ingested food or beverages (except water) 1 hour before the procedure and will not have performed oral hygiene within 2 hours before the procedure. The child will be instructed to swallow prior to the collection and then instructed not to swallow, allowing the saliva to drain between the lips (which will be separated) into a test tube (aspirator) connected to a 15-mL Flacon tube positioned near the mouth.^[30]^ Collection time will be 5 minutes. The volume of saliva will be measured and the salivary flow rate will be determined (mL/min). Salivary flow values will be analyzed based on the values below^[31]^ (Table 1).

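### Salivary IgA is compared before and after laser only as a concentration, on saliva left after 1 mL goes to titration, so both its value and its availability depend on flow

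*Protocol article*

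**What the plan says.** All of the laboratory steps are in section 2.8 of the protocol article.

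- Resting saliva is collected for a fixed time, not to a fixed volume: "Collection time will be 5 minutes". Flow in mL/min is worked out from the volume obtained.
- The first call on that volume is the titration for buffering capacity: "One aliquot (1 mL) of saliva will be transferred immediately to a small tube".
- IgA gets what is left: "The remaining saliva will be stored in Eppendorf tubes and frozen at –20 °C until the analysis of salivary IgA".
- IgA coverage is stated as complete: "Concentrations of salivary IgA in all samples will be measured using a commercial Enzyme-Linked Immunosorbent Assay (ELISA) kit".
- The measure is a concentration: "Salivary IgA (μg/mL) in each sample will be calculated using a standard curve". It is to be read against the reference values in Table 2 (not shown).

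Section 2.9 names flow and IgA as the quantities compared before and after laser, using ANOVA and Tukey's contrasts. Buffering capacity is not in that comparison.

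The Background says that laser makes the major salivary glands produce more saliva, that it contributes to higher immunoglobulin levels, and that malnutrition can reduce flow.

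The article names no IgA output per minute. It also does not say which assay has priority when a sample is short.

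**The concern.** Concentration is output per minute divided by flow per minute. The plan expects the intervention to raise flow, which is the denominator. A before/after change in μg/mL therefore cannot be read as a change in the amount of IgA delivered to the mouth. A fall may be dilution alone, and no change may conceal a rise in output.

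Separately, the order in which the sample is used ties the availability of one laser outcome (IgA) to the value of the other (flow). If short samples occur, they come from the children with the least saliva. If laser raises flow, there will be more of them before treatment than after. The assay served first is not in the laser comparison; the one served last is.

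The order of use has to be settled before collection begins, because saliva consumed in titration cannot be recovered by a later analysis plan.

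**Working it through.** The plan gives no figure of its own on this point. Its only computed figure, the sample of 50 in section 2.3.1, plays no part here except as a denominator.

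**1. Dilution.** Concentration = output ÷ flow. If output is unchanged and flow rises by a fraction g, concentration changes by 1/(1+g) − 1.

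| Flow rise | Concentration change | Concentration × flow |
|---|---|---|
| 20% | 1/1.2 − 1 = −16.7% | unchanged |
| 30% | 1/1.3 − 1 = −23.1% | unchanged |
| 50% | 1/1.5 − 1 = −33.3% | unchanged |

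Conversely, if output and flow both rise by 20%, concentration changes by 1.2/1.2 − 1 = 0, so a real rise in output does not show.

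**2. Volume left for IgA.** Inputs from section 2.8: collection time 5 min, titration aliquot 1 mL. Residual = 5 × flow − 1 mL, which reaches zero at 1/5 = 0.20 mL/min.

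| Flow (mL/min) | Collected (mL) | Left for IgA (mL) |
|---|---|---|
| 0.20 | 1.00 | 0 |
| 0.25 | 1.25 | 0.25 |
| 0.30 | 1.50 | 0.50 |
| 0.40 | 2.00 | 1.00 |

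**3. How many samples this could affect.** The article shows no flow distribution, so this step is assumption throughout. Take flow as lognormal with CV 50%, so the log-scale SD is s = √ln(1 + 0.5²) = 0.472. The share with nothing left is Φ[(ln 0.20 − ln median)/s].

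| Assumed median (mL/min) | Share with nothing left | Of 50 children |
|---|---|---|
| 0.20 | 50% | 25 |
| 0.25 | 32% | 16 |
| 0.30 | 20% | 10 |
| 0.40 | 7% | 4 |
| 0.50 | under 3% | 1 |

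Varying the CV from 40% to 60% at a median of 0.30 gives 7 to 12 of 50 before laser, and 3 to 6 after an assumed 25% rise in flow.

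**4. What selective loss does to the concentration comparison.** Paired samples were simulated with CV 50%, a within-child correlation of 0.6 in log flow, IgA output unaffected by laser, and flow up 25%. The true concentration ratio is 1/1.25 = 0.80.

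| Assumed median (mL/min) | IgA available before / after / both | Ratio, all available samples | Ratio, complete pairs |
|---|---|---|---|
| 0.20 | 50% / 68% / 43% | 0.91 | 0.86 |
| 0.30 | 80% / 91% / 77% | 0.86 | 0.83 |
| 0.50 | 97% / 99% / 97% | 0.81 | 0.81 |

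With no change in flow, the simulated ratio is 1.00 however many samples are lost. In this model, selection does not create a difference by itself. It alters the size of the difference once flow moves, and less so in a paired analysis.

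**The case against.** *Concentration is a legitimate outcome.* It is what the assay yields, it has reference values in Table 2, and the article's hypothesis is about immunoglobulin levels. This stands. A reader might infer that the IgA result will point the wrong way or carry a bias of 17% to 33%. The documents do not support that: those figures describe unchanged output, whereas the Background expects laser to raise IgA too. What remains is that concentration alone cannot separate the two effects.

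*Flow is not ignored.* It is compared beside IgA in section 2.9, so dilution would be visible to a careful reader. That also stands. But seeing both changes side by side does not give an estimate or a test of the change in output.

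*Secretion rate could be left to an analysis plan.* The derived variable could. The order of laboratory use could not, and the article states that order.

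*The article does not say that low-flow children yield no IgA value.* This is correct. A child with less than 1 mL cannot supply the aliquot, and the text does not send the whole short sample to titration. The loss is inferred from following the stated order. The supportable statement is that this order and the promise to assay every sample cannot both be kept at or below 0.20 mL/min.

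*The extent is unknown.* This stands in full. The values in Table 1 and the kit's minimum volume are not shown. It would also be too strong to say that low-flow children are the target population: the aim concerns malnourished children, and low flow is not an entry criterion.

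**Conclusion.** The point holds in two limited parts.

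First, the only stated IgA measure mixes output with dilution in a trial whose intervention is expected to raise flow. That follows from the definition of concentration. The falls of 17% to 33% for flow rises of 20% to 50% apply only if output is unchanged, and they are not a forecast.

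Second, the stated order of use leaves nothing for IgA at or below 0.20 mL/min, which contradicts complete IgA coverage and makes availability depend on flow. The threshold is arithmetic from the article. The frequency is not: it ranges from half of samples to under 3% across assumed medians of 0.20 to 0.50 mL/min. If nearly all children flow well above 0.20 mL/min, this part is minor and only the first remains.

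The change should be made, because it costs little and the laboratory order cannot be corrected afterwards. The case does not rest on any claim that the IgA result is bound to mislead.

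**What to change.** - **Outcome.** In the before/after comparison of section 2.9, analyse IgA secretion rate (concentration in μg/mL × flow in mL/min = μg/min) alongside concentration. Keep concentration for reading against Table 2. This needs no new measurement, since flow and concentration come from the same collection.
- **Order of use.** After recording the volume, set aside the small ELISA aliquot first. Titrate only when the full 1 mL still remains; otherwise record buffering capacity as missing. Scaling the acid to a smaller volume is not advised, because section 2.8 reads the result against fixed pH bands and nothing in the article shows that they stay valid for other volumes.
- **Reporting.** State the minimum volume for the assay, and report how many samples lacked IgA or buffering at each visit.

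The cost is one derived variable and a reordered bench step. The downside is that buffering capacity will be missing in some low-flow children. With an ELISA aliquot of a mL, titration needs a flow of at least (1 + a)/5 mL/min, slightly above 0.20. The flow-dependent gap thus moves to a measure that serves the secondary description of saliva and is not part of the laser comparison.

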**Figure 1 F1:**
[figure not shown]
Schedule of enrolment, interventions, and assessments.

**Table 2 T2:**
[figure not shown]
Normal IgA values in saliva of Brazilian children.

The data will be analyzed using Analysis of Variance (ANOVA) and Pearson's correlation test (*α* = 0.05). The Statistical Package for the Social Sciences (SPSS) (IBM Corp. Released 2012. IBM SPSS Statistics for Windows, Version 21.0. Armonk, NY: IBM Corp) version 15.0 will be used for all analyses.

### Administration of low level laser

2.9

Low-level laser will be administered using the Photon Lase III device (DMC Equipamentos LTDA, São Paulo, Brazil). Laser will be administered for 10 seconds on 4 intraoral points and 4 extraoral points in the region of the parotid glands bilaterally as well as 1 intraoral point and 1 extraoral point in the regions of the submandibular and sublingual glands. The first session will occur after the collection of saliva. The second and third sessions will be performed 7 and 14 days after the first session, respectively. The final saliva collection will be performed after the third laser session.^[34,35]^

The laser will be adjusted according to the following parameters: Central wavelength (nm) = 808; spectral band width (FWHM) (nm) = 2; operational mode = continuous; mean radiant power (mW) = 100; polarization = randomized; aperture diameter (cm) = 0.2; irradiation at aperture (mW/cm^2^) = 2500; beam profile = multimodal; beam spot on target (cm^2^) = 0.04; irradiation at target (mW/cm^2^) = 2500; exposure time (s) = 40; Radiant exposure (J/cm^2^) = 100.0; radiant energy (J) = 4; number of points irradiated = 10; irradiated area (cm^2^) = 0.40; application method = Contact; number of treatment sessions = 3; frequency of treatment sessions per week = 1; Total radiant energy (J) = 40.

The salivary flow rate and salivary IgA will be compared before and after of each laser application (after 7 and 14 days) and correlation with the malnutrition will be established. The results will be analyzed using ANOVA and Tukey's contrast test. The level of significance will be 5%.

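### Section 2.9 gives two incompatible laser exposure times, 10 s in the text and 40 s in the parameter list; the listed dose needs 40 s per point

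*Protocol article*

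**What the plan says.** Both statements are in the protocol article, section 2.9 (Administration of low level laser).

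- **Narrative sentence.** "Laser will be administered for 10 seconds on 4 intraoral points and 4 extraoral points" for the parotid region, "as well as 1 intraoral point and 1 extraoral point in the regions of the submandibular and sublingual glands". That is 4 + 4 + 1 + 1 = 10 points. The words 'per point' do not appear.
- **Parameter list, next paragraph.** It opens with "The laser will be adjusted according to the following parameters" and gives 100 mW mean power and then "beam spot on target (cm^2^) = 0.04; irradiation at target (mW/cm^2^) = 2500; exposure time (s) = 40". It continues "exposure time (s) = 40; Radiant exposure (J/cm^2^) = 100.0; radiant energy (J) = 4; number of points irradiated = 10", then an irradiated area of 0.40 cm², three sessions at one per week, and finally "Total radiant energy (J) = 40". The total is not labelled as per session or per course.

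Both are written as instructions, both cover the same ten points, and no text says which time governs.

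**The concern.** Exposure time and power together determine the energy delivered, so two exposure times mean two treatments. The primary aim is the effect of this laser on the children's saliva, and nothing else is given as treatment. An operator who follows the sentence and one who follows the list would give different doses to children aged 1 to 5 years. Any result could then be reported against a dose that was not delivered. If operators followed different lines, doses would also be mixed within the sample. The question is whether some reading makes the two times agree and, if not, how far apart the doses are.

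**Working it through.** **Inputs (all from section 2.9).** Power 100 mW = 0.1 W; irradiance at target 2500 mW/cm² = 2.5 W/cm²; spot area 0.04 cm²; 10 points; times of 10 s (sentence) and 40 s (list).

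**Formulas.** Energy per point = power × time. Radiant exposure = irradiance × time = energy ÷ spot area. Energy per session = energy per point × number of points.

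**Reproducing the listed dose at 40 s per point.**
- Energy: 0.1 × 40 = 4 J (listed: 4 J)
- Radiant exposure: 2.5 × 40 = 100 J/cm²; also 4 ÷ 0.04 = 100 (listed: 100)
- Session energy: 10 × 4 = 40 J (listed: 40 J)
- Area: 10 × 0.04 = 0.40 cm², and 0.40 × 100 = 40 J (listed: 0.40 cm², 40 J)

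**Working back from each listed figure to a time.**
- 4 J ÷ 0.1 W = 40 s
- 100 J/cm² ÷ 2.5 W/cm² = 40 s
- 40 J ÷ (10 × 0.1 W) = 40 s

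**Dose under each reading of the two times, ten points.**

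| Reading | Time per point | Energy per point | J/cm² | Energy per session |
|---|---|---|---|---|
| Listed figures | 40 s | 4 J | 100 | 40 J |
| 40 s per point | 40 s | 4 J | 100 | 40 J |
| 10 s per point | 10 s | 1 J | 25 | 10 J |
| 40 s is the session total | 4 s | 0.4 J | 10 | 4 J |
| 10 s is the session total | 1 s | 0.1 J | 2.5 | 1 J |

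**Other attempts to reconcile.**
- 40 s as four points × 10 s: the four points sum to 4 J, but each spot still receives 25 J/cm² and ten points give 10 J.
- 10 s on the eight parotid points and 40 s on the other two: 8 × 1 + 2 × 4 = 16 J.
- Doubling points for the two sides (16, 18 or 20 points) at 10 s: 16, 18 or 20 J per session and 48, 54 or 60 J over three sessions. It also contradicts the listed count of ten.
- 40 J as the total over three sessions: 3 × 10 = 30 J at 10 s and 3 × 40 = 120 J at 40 s. Neither is 40 J, so the listed total fits only as a one-session figure at 40 s per point.

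**Size.** 40 ÷ 10 = 4. Irradiation per session is 10 × 40 = 400 s against 10 × 10 = 100 s.

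**The case against.** The best counter-argument is that the list is plainly the operative specification. It sets the device, and three dose figures corroborate its 40 s, while the 10 s stands alone in a narrative sentence. A reader who works from the list obtains a clear per-point dose, and under-dosing happens only if someone follows the sentence instead. If one setting is used for every child at this single centre, the before/after comparison is internally consistent whichever setting that is. This makes 10 s the likelier slip and confines the harm in that case to the stated dose, its reporting and its replication. It does not remove the conflict, because the document never says that the list prevails.

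Three narrower points also have merit.
- 'Per point' is inferred in the sentence, so the four-fold size depends on that reading. The existence of a conflict does not, since the other readings fail as well.
- The list is not consistent in every entry. A circular aperture of 0.2 cm diameter has an area of π × 0.1² ≈ 0.031 cm², which at 100 mW gives about 3183 mW/cm², not 2500. The agreement claimed here is therefore among the time, power, energy, point-count and stated spot-area entries. The J/cm² figures rest on the stated 0.04 cm²; the 4 J and 40 J do not depend on area.
- No listed dose figure is miscalculated. This is a contradiction between two statements of one quantity.

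The condensed format of an article is no defence, since nothing is missing: both values are printed, and they disagree.

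**Conclusion.** The concern holds. Section 2.9 prescribes two different exposure times for the same ten points, and only 40 s per point reproduces the listed energy, radiant exposure and total. On the per-point reading of the sentence the difference is four-fold: 1 against 4 J per point, 25 against 100 J/cm², and 10 against 40 J per session. This assumes the stated power, irradiance and spot area are right and that the unlabelled total refers to one session. The document cannot show which time was intended; the agreement among the dose figures favours 40 s. Because this is the dose of the sole intervention, it should be corrected before treatment starts.

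**What to change.** Confirm the intended device setting before the first child is treated, then state one time, explicitly per point.

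- **If 40 s:** replace the 10 seconds in the narrative sentence with 40 seconds per point. One number changes.
- **If 10 s:** restate four list entries as exposure time 10 s, radiant energy 1 J, radiant exposure 25 J/cm² and total radiant energy 10 J.

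In either case, labelling the total as per session would remove the remaining ambiguity. The cost is one check of the device setting and a text edit.

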**Methods::**

Mandatory inclusion criteria are diagnosis of malnutrition. The sample will consist of 50 men and women malnourished children aged 12 to 71 months. Saliva will be collected and the volume of saliva will be measured and the salivary flow rate will be determined (mL/min). Concentrations of salivary IgA in all samples will be measured using a commercial Enzyme-Linked Immunosorbent Assay (ELISA) kit. Low-level laser (laser diode) will be administered in the region of the parotid glands bilaterally as well as in the regions of the submandibular and sublingual glands.

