#### Characteristics and size

2.3.1

This cross-sectional study will use a sample of children aged 12 to 71 months of the 7th Administrative Region of Maceió. This region is one of the poorest region in Maceió. The children's parents/guardians will be interviewed at the CREN in the city of Maceió, state of Alagoas, Brazil. The sample size was estimated considering a prevalence of malnutrition of about 10% in children under 6 years old, with statistical power of 80% and 95% significance, resulting in a sample of 50 children.

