### Inclusion criteria

2.5

Children aged 1 to 5 years enrolled at the CREN in the city of Maceió whose parent/guardians signed as statement of informed consent agreeing to the participation of the children.

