#### Evaluation of nutritional status

2.7.1

The children will be weighed on a duly calibrated electronic anthropometric scale (capacity: 150 kg; precision: 100 g) barefoot and wearing light clothing in the presence of the mother or caregiver. Height will be determined using a non-flexible metric tape measuring 2 m in length (precision: 0.1 cm). The measurement will be performed twice and the mean will be used for the calculation of the indices. Using these measures, height for age and weight for age will be determined using the nutritional reference standards recommended by the World Health Organization, with a cutoff point (*Z* score) between +1 and –1 standard deviations (SD) of the median indicative of the ideal range, *Z* between –1 and –2 SD indicatives of mild malnutrition, *Z* between –2 and –3 SD indicatives of moderate malnutrition and *Z* >–3 indicative of severe malnutrition.^[29]^

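### Salivary flow and IgA are related to malnutrition by Pearson's correlation with no age term, although the children span 12 to 71 months

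*Protocol article*

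**What the plan says.** Section 2.8 (Saliva collection and analysis, the paragraph after Table 2) commits to "Analysis of Variance (ANOVA) and Pearson's correlation test" at α = 0.05. Section 2.9 (Administration of low level laser) adds that, besides the before-and-after comparisons of flow and IgA, "correlation with the malnutrition will be established". No other correlation method is named, so Pearson's is the natural reading. Neither section mentions a covariate, a partial correlation or age strata.

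Section 2.3.1 describes a "sample of children aged 12 to 71 months". Flow is expressed in mL/min and IgA in μg/mL. The text gives no age-standardised version of either, and the contents of Tables 1 and 2 are not visible.

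On the exposure, section 2.7.1 states that "height for age and weight for age will be determined using the nutritional reference standards recommended by the World Health Organization". Malnutrition therefore enters as Z scores that already take age into account, graded on a scale that includes an ideal range.

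On who enters, the Abstract and section 2.5 differ. The Abstract says "Mandatory inclusion criteria are diagnosis of malnutrition". Section 2.5 asks only for age, enrolment at the centre and consent: "Children aged 1 to 5 years enrolled at the CREN in the city of Maceió".

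**The concern.** A simple correlation compares children of very different ages as if age did not matter. Age can act in two ways. If saliva changes with age, and the Z scores of the enrolled children also drift with age, part or all of the observed coefficient reflects age; depending on the signs, this can create an association or hide one. If saliva changes with age but Z does not, age is unexplained variation in the outcome, and the coefficient is weaker than the association at a given age.

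Analysing the saliva of malnourished children and establishing the degree of malnutrition are both listed as secondary outcomes, at the end of the Background. The correlation is the stated step that joins the two. It is not the primary before-and-after laser comparison, which this point leaves untouched.

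**Working it through.** **Inputs.** From the article: n = 50 (Abstract and section 2.3.1), significance level 5% (section 2.9), Pearson's correlation (section 2.8). Assumed, because the article gives no figure: a two-sided test, the correlation of age with saliva, and the correlation of age with Z in the enrolled children.

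**The plan's own figure.** There is none to reproduce for this analysis. The sample size rests on a 10% prevalence and states no correlation. For orientation, the smallest correlation that 50 children detect with 80% power is tanh[(1.960 + 0.842)/√47] = tanh(0.409) = 0.39.

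**Case A: Z trends with age, and there is no association between Z and saliva at a given age.** The induced correlation is r = r(age, Z) × r(age, saliva). With d = atanh(r) × √(n − 3) = atanh(r) × √47, the false-positive rate is Φ(d − 1.96) + Φ(−d − 1.96). With r(age, saliva) = 0.4:

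| r(age, Z) | induced r | d | false-positive rate |
|---|---|---|---|
| 0 | 0 | 0 | 5.0% |
| 0.1 | 0.04 | 0.274 | 5.9% |
| 0.3 | 0.12 | 0.827 | 13.1% |
| 0.4 | 0.16 | 1.106 | 19.8% |

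**Case B: Z does not trend with age.** There is no confounding. The Pearson coefficient is the age-adjusted correlation times √(1 − r(age, saliva)²). With an age-adjusted correlation of 0.40 and r(age, saliva) = 0.5:

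- Observed r = 0.40 × √(1 − 0.25) = 0.40 × 0.866 = 0.346, about 0.35.
- Power at r = 0.40: d = 0.4236 × 6.856 = 2.904, and Φ(2.904 − 1.96) = 83%. Charging one degree of freedom for age (√46 in place of √47) gives d = 2.873 and 82%.
- Power at r = 0.346: d = 0.3613 × 6.856 = 2.477, and Φ(2.477 − 1.96) = 70%.

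**Check by simulation** (200,000 data sets of 50 children per setting, normal data, the usual t tests). Pearson's test rejected in 5.0%, 5.9%, 13.2% and 19.8% of data sets in the four rows of Case A. The age-adjusted test stayed between 4.9% and 5.0% throughout. In Case B power was 71% unadjusted and 83% adjusted, so the normal approximation above is within about a point.

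**The case against.** **The exposure is already age-standardised.** This is the strongest objection, and it stands as a limit on size. Standardisation is against the WHO reference, so it does not guarantee that Z is unrelated to age among children enrolled at one nutrition recovery centre. But the article shows no such trend, and without one the false-positive rate is the nominal 5%. A reader might infer that the correlation will be significant through age alone; the documents do not support that.

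**A condensed article may leave covariates to an analysis plan.** This is fair, and the text never excludes adjustment. However, the article does name the method, and that method as named has no place for age. The criticism is of a stated choice.

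**Range restriction.** A reader might go further and say that the coefficient is shrunk because only malnourished children enter. The article does not settle that: the Abstract requires malnutrition and section 2.5 does not. Even if entry is so limited, r is a valid description of the malnourished group, which is the group the aim concerns. What remains is narrower: under that limit r cannot be compared with r in wider populations. A slope can be, if the relation is linear, but it does not restore power, because without covariates the test of a slope and the test of Pearson's r are the same test.

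**Repeated samples.** A reader might also suppose that the several saliva samples per child will be pooled as independent rows. Nothing in the article says so, and no error rate should be attached to it. Stating one record per child simply closes the question.

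**Conclusion.** The point holds as one about age adjustment in a supporting analysis. The stated Pearson correlation ignores age across a range of almost five years, and adjusting for age is better in either case: it removes confounding if Z trends with age in this sample, and removes age-related noise from the outcome if Z does not.

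The size is uncertain. It runs from no inflation of false positives to roughly 20% under assumed correlations of up to 0.4 for age with both variables. Alternatively, it is a loss of about 12 percentage points of power (83% to 71%) under an assumed age–saliva correlation of 0.5 with no trend in Z. If age is unrelated to saliva, neither effect arises and the adjustment costs almost nothing. It is worth correcting, but it does not threaten the main laser comparison.

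**What to change.** Replace Pearson's correlation with linear regression, one record per child. Regress baseline flow and baseline IgA, and separately their change to the final collection, on continuous height-for-age Z. Repeat in a separate model with weight-for-age Z. Include age in months as a covariate in every model, and report each slope with its 95% CI. Two outcomes, two versions of each (baseline and change) and two indices give 2 × 2 × 2 = 8 slopes, best presented as supporting estimates and not as eight separate claims of significance.

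Reconcile the entry condition in the Abstract with section 2.5, so that the reader knows over which range of Z the slope was estimated.

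The cost is wording and one degree of freedom per model. Age is needed to compute the Z scores in any case, so no new data are required.

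### The before/after laser comparison is within child, but the named ANOVA with Tukey contrasts does not account for repeated measurements on the same child

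*Protocol article*

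**What the plan says.** Section 2.9 of the Protocol article sets the laser comparison: "The salivary flow rate and salivary IgA will be compared before and after of each laser application (after 7 and 14 days"). Saliva is taken before the first session, and a final collection follows the third, at 14 days. The outcome is thus measured at least twice in each child. The section adds a second aim, "and correlation with the malnutrition will be established", and then names the method: "The results will be analyzed using ANOVA and Tukey's contrast test", at the 5% level.

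Section 2.8 closes with a general statement, "The data will be analyzed using Analysis of Variance (ANOVA"), together with Pearson's correlation at alpha 0.05.

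Neither statement gives the type of ANOVA, and neither mentions pairing, repeated measures or a term for the child. Sections 2.1 and 2.3.1 call the study cross-sectional. No comparison arm is described, so the primary aim rests on change within the same children.

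The sample size in Section 2.3.1 was derived from prevalence: "The sample size was estimated considering a prevalence of malnutrition of about 10% in children under 6 years old". That section arrives at 50 children and gives no effect size, standard deviation or within-child correlation for saliva.

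**The concern.** Two measurements on one child are usually positively correlated, and these children range from 12 to 71 months of age, so they may well differ from one another in salivary flow and IgA. A before/after design gains precision by removing those differences from the error. ANOVA with Tukey's contrast, given without qualification in a study described as cross-sectional, is naturally carried out as a one-way analysis with visits as the groups, which puts the between-child variation back into the error.

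The comparison that answers the primary aim would then have confidence intervals that are too wide and a test that rejects too rarely, so a real change after laser could be reported as no change. Because the sample size was not based on a salivary outcome, nothing in the article shows spare power to absorb the loss.

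The malnutrition association raises a smaller question. The outcome is measured repeatedly, and the article does not say which value per child enters the correlation.

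**Working it through.** **Inputs.** From the article: n = 50 children (Section 2.3.1), 5% level (Sections 2.8 and 2.9), same children before and after laser (Section 2.9). Assumed, because the article does not give them: two-sided testing, within-child correlation rho from 0 to 0.7, and the size of the rise in SD units. The plan has no power figure for a salivary change, so there is none to reproduce.

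**Step 1: standard error.** Let sigma be the SD at one visit.
- True variance of the difference between two visit means: 2·sigma²·(1 − rho)/n.
- Variance used by one-way ANOVA with visits as groups: 2·sigma²/n.
- Ratio of standard errors: 1/sqrt(1 − rho).

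With n = 50 the one-way value is sqrt(2/50) = 0.200 SD at every rho.

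| rho | True SE (in SD) | Ratio |
|---|---|---|
| 0 | 0.200 | 1.00 |
| 0.3 | sqrt(1.4/50) = 0.167 | 1.20 |
| 0.5 | sqrt(1.0/50) = 0.141 | 1.41 |
| 0.7 | sqrt(0.6/50) = 0.110 | 1.83 |

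**Step 2: type I error.** With two visits, a nominal 5% one-way test rejects a true null in about 1.8% (rho 0.3), 0.5% (0.5) and 0.03% (0.7) of trials. With three visits, the simulated familywise rate of Tukey's test with visits as groups is about 1.5% at rho 0.3 and 0.3% at rho 0.5. With the within-child error term it stays at about 5%. The error is therefore in the conservative direction.

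**Step 3: power with three visits.** Simulation with n = 50, equal correlation between all visits, a linear rise, complete data and the Tukey contrast of day 0 against day 14:

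| Rise by day 14 | rho | Visits as groups | Within-child error |
|---|---|---|---|
| 0.4 SD | 0.3 | 34% | 51% |
| 0.4 SD | 0.5 | 31% | 68% |
| 0.4 SD | 0.7 | 27% | 90% |
| 0.5 SD | 0.3 | 56% | 73% |
| 0.5 SD | 0.5 | 58% | 87% |
| 0.5 SD | 0.7 | 60% | 98% |

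At rho = 0 the two analyses have the same power. As a share of the attainable power, the loss at 0.4 SD is 17/51 = 33%, 37/68 = 54% and 63/90 = 70%. At 0.5 SD it is 17/73 = 23%, 29/87 = 33% and 38/98 = 39%.

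**Step 4: power with two visits.** Noncentral t for the paired test; normal approximation for the one-way test applied to correlated data. At rho 0.3, 0.5 and 0.7:
- Rise of 0.4 SD: 51% against 65%, 51% against 79%, 51% against 95%.
- Rise of 0.5 SD: 73% against 83%, 77% against 93%, 83% against 99%.

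At each correlation the loss is smaller than with three visits.

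**The case against.** The best defence is that the article never says its ANOVA is for independent groups. Repeated-measures ANOVA is also ANOVA, Tukey-type contrasts can follow it, and a condensed article may leave the form to a fuller document. One-way ANOVA with Tukey would also be proper for comparing children across the malnutrition grades of Section 2.7.1, and the statement in Section 2.8 could be meant for that. Finally, any error is conservative, so it would not produce a false claim of laser benefit.

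Much of this stands. A reader might infer that the plan specifies an independent-groups analysis; the text does not. But the article does fix the test, the post-hoc procedure, the level and the software. It attaches ANOVA and Tukey to the section that defines the before/after comparison, and nowhere recognises that children are measured more than once. A conservative error still matters in a study of 50 children, where the risk is a false null.

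Four other inferences are tempting and are not supported:
- **Most of the power is lost.** This is true only for small effects with high assumed correlation.
- **Three collections are certain.** The text describes a first and a final collection; a day-7 collection is suggested by the comparison wording but not spelled out, and the schedule figure is not shown.
- **Visits are pooled in the Pearson test.** Pooling would make p-values too small, but one value per child fits the text equally well.
- **Age is an uncontrolled confounder.** Malnutrition is graded on age-referenced Z-scores, and age barely changes over 14 days within a child. Residual confounding of the association is possible but not shown.

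**Conclusion.** The concern holds in this form: the analysis named for the primary-aim comparison does not account for repeated measurements on a child, and a within-child analysis would be better at almost no cost. Carried out with visits as groups, it would overstate the standard error by 1.20 to 1.83 for rho between 0.3 and 0.7. Day 0 against day 14 power at a 0.4 SD rise would fall by about 17 to 63 percentage points with three visits, or 14 to 44 with two. At rho = 0 nothing is lost.

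These sizes rest on assumed correlations and effects, equal SD and correlation across visits, and complete data. They show what is at stake and are not a forecast for this trial. The conclusion does not extend to a claim that the plan prescribes independent groups, or that its malnutrition correlation is invalid. The wording should be corrected before analysis.

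**What to change.** In Section 2.9, replace the ANOVA and Tukey sentence with a repeated-measures ANOVA or a linear mixed model, with child as random effect and visit as fixed effect, and take multiplicity-adjusted within-child contrasts from that model. If saliva is collected only twice, a paired analysis is enough; state the number of collections so that the choice is clear. Make the general statement in Section 2.8 consistent, and say which comparisons, if any, are between children (for example across malnutrition grades).

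For the malnutrition association, state that each child contributes one record, for example the child's change in flow or IgA against the baseline Z-score. A log transform and further covariates such as age or baseline value are optional.

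The cost is analysis wording only: no new data, visits or children are needed.
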